### Control group

Participants who will be randomized to the control group will receive the usual care, which follows clinical guidelines [23].

For patients admitted to one out of three wards, an outpatient visit will be scheduled one month after discharge. However, no follow-up will be planned for patients discharged from the other two wards.

### Outcomes measured

Four aspects of feasibility will be the focus of the outcomes’ measurement [22]:-Process: evaluates the feasibility of the study's fundamental steps (e.g. recruitment rate).-Resource: investigates potential time and resource problems during the study (e.g. retention rate, adherence to the coaching intervention, adherence to the telemonitoring program, and the amount of time spent by nurses each week on coaching interventions).-Management: examines possible issues related to patient and data handling (e.g. frequency of calls made by patients to the nurse, the acceptability of the intervention to patients, completeness of data collection).-Scientific value: describes how treatment safety, response, effect, and effect variance are evaluated (patient's self-care capacity, self-efficacy, quality of life, somatic perception of the disease, emotional and psychological well-being, mortality, all-cause hospital admissions, HF-related hospital admissions, etc.)

## Data collection

To ascertain whether the intervention is acceptable and feasible, both quantitative and qualitative data will be obtained. Quantitative data will be collected via telephone by an assessor not involved in the coaching intervention and blinded to the group assignment.

### Quantitative data

Table 2 outlines the types and timeframes of the variables measured.

**Table 2 tbl0002:** Variables and timeframes for measurements.

	T0 (baseline)	T1 (3 months)	T2 (4 months)	T3 (6 months)
Recruitment rate				**×**
Retention rate				**×**
Adherence to the coaching intervention			**×**	
Adherence to telemonitoring program			**×**	
Weekly time dedicated to coaching intervention but the nurse			**×**	
Number of returned questionnaires	**×**	**×**		**×**
Semi-structured individual interviews			**×**	

Sociodemographic information	**×**			
Comorbidities	**×**			
Number of medications	**×**	**×**		**×**
Left ventricular ejection fraction	**×**			
New York Heart Association (NYHA) Functional Classification	**×**		**×**	
B-type natriuretic peptide (BNP) dosing	**×**			
Number of hospital admissions in the past two years	**×**			
Anthropometrical indicators	**×**	**×**		
Health literacy	**×**			
Cognitive status	**×**	**×**		**×**
Vaccinations	**×**	**×**		**×**
Smoking habits	**×**	**×**		**×**
Heart failure-related hospital readmissions		**×**		**×**
All-cause hospital readmissions		**×**		**×**
Outpatient visits		**×**		**×**
General Practitioner visits		**×**		**×**
Emergency Department visits		**×**		**×**
Quality of life	**×**	**×**		**×**
Self-care capabilities	**×**	**×**		**×**
Self-efficacy	**×**	**×**		**×**
Heart failure somatic perception	**×**	**×**		**×**
Anxiety	**×**	**×**		**×**
Depression	**×**	**×**		**×**
Mortality		**×**		**×**

Sociodemographic and clinical data will be collected:

*Sociodemographic characteristics:* gender, age, education level, marital status, social network, employment status, financial level.

*Clinical information*: comorbidities according to the Cumulative Illness Rating Scale (CIRS) [26], anthropometrical indicators*,* left ventricular ejection fraction (considered reduced for values 〈40 %; mildly reduced between 41 %- and 49 %; preserved if 〉 50 %), B-type natriuretic peptide (BNP) dosage; the number of medications, number of hospital admissions in the past two years, staging of HF according to New York Heart Association (NYHA) Functional Classification, level of health literacy according to the European Health Literacy Survey (short-short form, English version) (HLS-EU-Q6) [27], Mini-COG [21] smoking habit, weight and height, COVID-19 and pneumococcal vaccinations.

The following outcomes will be measured:-*Recruitment rate:* the proportion of patients who agreed to participate relative to those who fulfilled the inclusion criteria.-*Retention rate*: the proportion of patients who complete the study relative to those who consent to participate.--*Adherence to the coaching intervention:* the number of coaching phone calls scheduled relative to those actualized.-*Adherence to telemonitoring program:* the proportion of days during which vital signs were measured and sent by the system relative to the total duration of the intervention.-*Weekly time dedicated to coaching intervention by the nurse* (in hours).-*Completeness of data collection:* the number of returned questionnaires.-*Number of weekly calls made by patients to the nurse.*-*Quality of life*: Quality of life is a value that integrates objective (physical health, personal circumstances, social relationships, social and economic influences) and subjective indicators (such as how the individual responds to objective conditions), related to various dimensions of life and personal values [28]. This outcome will be assessed using the Italian version of the SF-12 scale [29]. This is a multidimensional scale consisting of 12 questions related to physical functioning, limitations due to physical health or emotional factors, energy and fatigue, emotional well-being, social activities, pain, and general health perception. The scale collects self-report data using a Likert scale. The score for each subscale will be standardized on a 0–100 scale, where higher values indicate better quality of life.-*Self-care capacity*: The self-care capacity of the patient encompasses three dimensions: self-care maintenance, symptom perception, and self-care management [30]. Self-care maintenance reflects the active commitment and responsibility for one's own care, as well as the behaviors adopted to maintain physical and emotional stability (e.g., adherence to therapy). On the other hand, symptom perception refers to the ability to respond to signs and symptoms of disease exacerbation when they occur, such as by searching for help (self-care management) [30]. The self-care capacity will be evaluated using the Italian version of the Self-Care of Heart Failure Index (SCHF v. 7.2) [31]. The tool consists of three different scales: self-care maintenance (10 items), symptom perception (11 items), and self-care management (8 items) producing a standardized score of 0–100, where higher values refer to the greater self-care capacity. A score ≥70 indicates adequate self-care capacity.-*Self-Efficacy Scale:* Self-efficacy perception refers to the individual's belief in their ability to achieve certain goals because of their actions, regardless of the challenges and difficulties they may face [32]. Self-efficacy is a mediator of self-care capacity [32]. A scale consisting of 10 items using a 5-response Likert scale will be utilized [33].-*Heart Failure Somatic Perception Scale v.3* (HFSPS) [34]. HF is a complex clinical syndrome characterized by several signs and symptoms, including shortness of breath, fatigue, and peripheral fluid accumulation [23]. To measure this outcome, we will employ a scale comprising four factors, which evaluate the presence and impact of 18 typical signs and symptoms of HF experienced by the patient in the preceding week. Each item has 6 response options ranging from 0 (I do not have this symptom) to 5 (extremely severe), with a range from 0 to 90, where high scores lead back to a greater impact of symptoms on the patient.-*Geriatric Depression Scale short version* (GDS) [35] for detecting depressive symptoms of the elderly. It consists of 15 questions involving a dichotomous response (yes/no). Ten questions are indicative of depression for positive responses, while the remaining five (items 1, 5, 7, 11, 13) for negative responses. Scores 0–4 are considered normal, depending on age and education; scores between 3 ± 2 are associated with the absence of depressive symptoms, 7 ± 3 mild depression, and 12 ± 2 depression.-*Hamilton Anxiety Scale* [36]: for the assessment of anxiety symptoms (psychological and somatic). The scale consists of 14 items, rated on a 4-point Likert scale (0=not present; 4= severe), with a range of total score from 0 to 56, where values ≤ 17 indicate mild anxiety, 18–24 moderate anxiety and ≥ 25 severe anxiety.-*Hospital readmissions at 90- and 180- days* after hospitalization for all causes and HF-related, Emergency Departments visits, outpatient visits, General Practitioner visits, and mortality.

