## Abstract

Poor treatment adherence and lack of self-care behaviors are significant contributors to hospital readmissions of people with heart failure (HF). A transitional program with non-invasive telemonitoring may help sustain patients and their caregivers to timely recognize signs and symptoms of exacerbation.

We will conduct a Randomized Clinical Trial (RCT) to evaluate the feasibility and acceptability of a 6-month supportive intervention for patients discharged home after cardiac decompensation. Forty-five people aged 65 years and over will be randomized to either receive a supportive intervention in addition to standard care, which combines nurse-led telephone coaching and a home-based self-monitoring vital signs program, or standard care alone. Four aspects of the feasibility will be assessed using a mixed-methods approach: process outcomes (e.g., recruitment rate), resources required (e.g., adherence to the intervention), management data (e.g., completeness of data collection), and scientific value (e.g. 90- and 180-day all-cause and HF-related readmissions, self-care capacity, quality of life, psychological well-being, mortality, etc.). Participants will be interviewed to explore preferences and satisfaction with the intervention. The study is expected to provide valuable insight into the design of a definitive RCT.

Specifications table

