### Intervention group

A supportive program will be provided in addition to standard care, consisting of 1) a pre-discharge educational meeting, 2) telephone nurse-led coaching sessions and 3) home telemonitoring of vital signs.(1)*Pre-discharge educational meeting.* After the patient is deemed stable by the clinicians, an in-hospital educational intervention will be provided by a trained nurse not involved in the clinical pathway. Family members will be invited to participate but attendance will not be mandatory. Key topics of self-care management recognized by the European Society of Cardiology will be discussed, including the importance of physical activity, rest and sleep quality, fluid restriction, a healthy diet, medication adherence, the advantages of immunization, smoking cessation, psychological issues, need for formal and informal support [23].During the meeting, the nurse will use the Transtheoretical Model of Prochaska & DiClemente [24] to identify the individual's priority goals and motivation for change, thus initiating the coaching session. The model recognizes five stages of change:-pre-contemplation: not yet recognizing the existence of problematic behavior that requires change.-contemplation: recognizing the presence of a problem but not yet being prepared, certain, or confident about the desire or ability to enact a change.-determination: preparing to change behavior.-action: taking action to change behavior.-maintenance: maintaining the changed behavior.(2)*Telephone nurse-led coaching sessions.* In this phase, patients will be encouraged to focus on their values and progress towards their goals. The intervention will be tailored based on the stage for change and personal difficulties reported by the individual during the initial meeting (e.g. if the patient is in the pre-contemplation phase, the nurse will adopt an informative approach). The scheduled sessions will occur weekly during the first month and then transition to twice a month thereafter. If the person is unavailable, a second attempt will be made the following day at the same time.(3)*Home telemonitoring of vital signs*. Patients will receive education on measuring weight, blood pressure, heart rate, and oxygen saturation at rest every morning before breakfast. All participants will be provided with a telemonitoring system connected to a smartphone, which acts as a gateway and transmits data to a web platform via Bluetooth.

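### Table 2 schedules adherence and nurse time at month 4 only, although the programme lasts 6 months and telemonitoring adherence is defined over its full length

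*Protocol article*

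**What the plan says.** The Abstract sets out to "evaluate the feasibility and acceptability of a 6-month supportive intervention". Under Intervention group, the coaching calls are planned as follows: "The scheduled sessions will occur weekly during the first month and then transition to twice a month thereafter". No end date is given there. The Specifications table gives the later interval as one call every two weeks.

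Under Quantitative data, Table 2 has columns for baseline, 3, 4 and 6 months. Three rows are marked in the 4-month column alone: "Adherence to the coaching intervention", "Adherence to telemonitoring program" and "Weekly time dedicated to coaching intervention but the nurse". The individual interviews sit in the same column. Recruitment and retention are marked at 6 months.

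The outcome definitions that follow the table give telemonitoring adherence as "the proportion of days during which vital signs were measured and sent by the system relative to the total duration of the intervention". Coaching adherence is "the number of coaching phone calls scheduled relative to those actualized", with no period named. Nurse time is in hours per week, also with no period named.

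**The concern.** Telemonitoring adherence has a denominator of the whole programme but is scheduled for measurement when two months remain. An analyst who follows the table must either break the definition or produce a figure that cannot reach 100%. The other two measures have no such conflict in their definitions, but on the schedule shown they too stop at month 4.

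The Aim of the study is the feasibility and acceptability of telemonitoring plus coaching. Outcomes measured lists these three items among the resource outcomes, and Limitations says that the programme's success depends on adherence. Whether patients keep up daily readings and calls to the end is therefore a central question. The data come from only 15 intervention patients. According to the Specifications table, those data may be pooled with the definitive trial if the intervention is validated without substantial correction.

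**Working it through.** The plan states no adherence figure, so there is none to reproduce.

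**Inputs**
- Programme length: 6 months, about 183 days (Abstract).
- Measurement point: 4 months, about 122 days (Table 2).
- Calls: weekly in month 1, taken as 4. After that, either two a month (Intervention group) or one every two weeks (Specifications table).

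**Is the column placement reliable?** The interview row is marked at T2, and the Qualitative data section separately places the interviews after 4 months. The columns have therefore been read correctly.

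**Does the programme end at month 4?** Nothing says so. The interview guide (Table 3), used at month 4, asks about telephone support as something still being received.

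**Telemonitoring adherence**
- Month-4 count over the 6-month denominator: maximum = 122/183 = 4/6 = 66.7%.
- On that calculation, a patient who measures on 90% of days shows 0.90 × 4/6 = 60.0%, and one who measures on 80% of days shows 53.3%.
- Month-4 count over a 4-month denominator: no ceiling, but 2/6 = 33.3% of the programme is unobserved.
- Illustration with assumed values: take 90% in months 1 to 4. If measuring then stops, the 6-month figure is (4 × 0.90 + 2 × 0)/6 = 60%. If it falls to 60%, the figure is (4 × 0.90 + 2 × 0.60)/6 = 80%. If it is maintained, the figure is 90%. A 4-month denominator reports 90% in all three cases.

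**Scheduled calls**
- Two a month: 4 + 2 × 3 = 10 by month 4, and 4 + 2 × 5 = 14 by month 6. Outside the schedule: 4/14 = 28.6%.
- Every two weeks: 4 + 6 = 10 by week 17, and 4 + 11 = 15 by week 26. Outside the schedule: 5/15 = 33.3%.
- If month 1 held five calls at two a month thereafter, the share would be 4/15 = 26.7%.

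**Nurse time** has no ceiling. The same two months are simply left out.

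**The case against.** The best defence is that a mark in Table 2 may show when a running record is tallied, not the window it covers. Weekly nurse time has a single mark although it must be recorded throughout, and recruitment is marked at 6 months although patients enter at discharge. A month-4 tally also has a sensible use, because the interviews at that visit ask about daily measuring and telephone support. This stands, and it means that the month-4 value is not itself the defect. It does not supply the missing 6-month value, and it does not reconcile the table with the written denominator.

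Three stronger readings are tempting, but the documents do not support them:
- A reader might infer that all three measures are capped at 67%. Only telemonitoring adherence is defined against total duration, and the cap arises only if someone puts a 4-month count over 6 months, which no section instructs.
- A reader might infer that data from months 5 and 6 are lost. Readings are transmitted to a web platform, so they may well be retrievable. What is missing is a planned report of them.
- A reader might infer that stopping at month 4 overstates nurse workload because calls are front-loaded. With two calls a month the rates are 10/4 = 2.5 and 14/6 = 2.33 per month, but with calls every two weeks they are 10/4 = 15/6 = 2.5. Any bias therefore depends on which wording is applied. Calls per month are also not the defined outcome, which is hours per week.

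The protocol shows no adherence threshold that a distorted figure would trip, and retention is assessed at 6 months. That limits the consequence, but retention does not show whether patients kept measuring.

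**Conclusion.** The point holds as an internal inconsistency, together with a gap in the measurement schedule. For telemonitoring adherence, the timing in Table 2 and the definition cannot both be followed. Depending on the denominator chosen, a fully adherent patient would be reported as 67% or 100%. For all three measures, no value covering months 5 and 6 is scheduled. That omits a third of the programme and roughly 29% to 33% of scheduled calls, so the study as scheduled would not report whether adherence was sustained to the end.

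This assumes that the intervention runs the full 6 months stated in the Abstract, that month 1 contains four calls, and that Table 2 is the complete schedule for these measures. The size of any late decline is unknown, and the figures given for it are illustrations only.

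**What to change.** In Table 2, mark coaching adherence, telemonitoring adherence and weekly nurse time at T3, each computed over the whole 6 months. If the month-4 values are wanted beside the interviews, keep the T2 marks but label them interim and give them their own 4-month denominator. State the period covered in the definitions of coaching adherence and nurse time as well. Tabulating adherence by month would make any decline visible.

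The cost is a table edit and a little more tabulation, with no extra patient contact. This assumes that platform and call records continue to month 6, which the 6-month intervention implies but the article does not state.

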**Table utbl0001:** 

Subject area:	Medicine and Dentistry
More specific subject area:	*Geriatric care*
Name of your protocol:	INTERCOACH
Reagents/tools:	*Mini-COG* *Edmonton Symptom Assessment System (ESAS)* *Cumulative Illness Rating Scale (CIRS)* *European Health Literacy Survey* *SF-12 Questionnaire* *Self-Care Of Heart Failure (SCHF v. 7.2)* *Heart Failure Somatic Perception Scale v.3 (HFSPS)* *Self-Efficacy Scale* *Geriatric Depression Scale short version* *Hamilton Anxiety Scale*
Experimental design:	*A prospective, open label randomized controlled feasibility study will be conducted, with a 1:2 ratio between intervention and control groups. Participants assigned to the intervention group will receive the following educational program in addition to standard care: 1) an in-person educational intervention before discharge, following the recommendations of the European Society of Cardiology; 2) a nurse-led telephone coaching service (once a week for the initial month, followed by sessions every two weeks); 3) a daily home-based self-telemonitoring system for weight, blood pressure, heart rate, and oxygen saturation. Vital signs will be transmitted to a platform and remotely monitored by a nurse. A structured intervention protocol will be activated based on the patient's clinical conditions.*
Trial registration:	*The study protocol has been registered in the Clinicaltrials.gov:**NCT06285565*
Ethics:	*The study protocol was submitted and approved by the Ethics Committee of Maggiore della Carità Hospital of Novara in December 2023 (*CE390/2023). *The study will adhere to the Ethical Principles of the Declaration of Helsinki, as well as the European Union Standards of Good Clinical Practice* *The data from the feasibility study will be combined with those from the definitive study if it validates the suggested intervention and no substantial corrections will be required.*
Value of the Protocol:	(1) *This protocol is important to inform the design of a definitive RCT, aimed to assess the effectiveness of a remote nurse-led coaching intervention with a home telemonitoring program.* (2) *Given the complexity of the supportive intervention, it is crucial to involve patients in the research process and to collect their preferences regarding the intervention.* (3) *3) This feasibility study is important to define a successful care plan that guarantees follow-up for patients with heart failure*.

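### Coaching adherence is defined with its two terms swapped, so taken literally it rises as adherence falls

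*Protocol article*

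**What the plan says.** The list of outcome definitions under Quantitative data gives adherence to the coaching intervention as "the number of coaching phone calls scheduled relative to those actualized". Three other outcomes in that list use the same construction:

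- Recruitment rate: "the proportion of patients who agreed to participate relative to those who fulfilled the inclusion criteria".
- Retention rate: "the proportion of patients who complete the study relative to those who consent to participate".
- Adherence to telemonitoring: "the proportion of days during which vital signs were measured and sent by the system relative to the total duration of the intervention".

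The Intervention group section sets the call schedule: "The scheduled sessions will occur weekly during the first month and then transition to twice a month thereafter". It also foresees missed calls: "If the person is unavailable, a second attempt will be made the following day at the same time". Table 2 marks coaching adherence at T2 (4 months) only. Outcomes measured names it among the Resource outcomes. Aim of the study makes the feasibility and acceptability of the combined telemonitoring and coaching programme the primary aim.

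**The concern.** In the three comparison definitions the achieved part stands before the words of comparison and the whole stands after them, so the whole is the denominator. Coaching adherence has the planned number first and the completed number second. Read consistently, its denominator is the number of calls that took place.

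Such a ratio runs the wrong way for something called adherence: a higher value means worse adherence. It also runs opposite to telemonitoring adherence, the measure that will naturally be reported beside it. A reader who takes a larger coaching figure as better would draw the wrong conclusion about one of the components that this study is meant to test. The Limitations section says that success depends on adherence to both the educational and the telemonitoring parts, so this outcome is not incidental.

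**Working it through.** The article states no adherence figure, so there is none to reproduce. The check applies the written rule to the article's own schedule.

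**Inputs**
- Scheduled calls, S, from the Intervention group section, taking the first month as 4 weeks (an assumption). To month 4: 4 + 2 × 3 = 10. To month 6: 4 + 2 × 5 = 14.
- Completed calls, C, varied from all to none.
- Patients concerned: 15 in the intervention arm (Sample size section).

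**Formulas**
- As written: S / C.
- Same direction as the neighbouring definitions: C / S.

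**One patient, S = 10 (month 4)**

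| C | S / C as written | C / S |
|---|---|---|
| 10 | 1.00 | 100% |
| 8 | 1.25 | 80% |
| 5 | 2.00 | 50% |
| 1 | 10.0 | 10% |
| 0 | undefined | 0% |

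If completed calls cannot exceed scheduled calls, S / C is never below 1, has no upper limit short of the undefined case, and increases with every missed call. C / S stays between 0 and 1 and is defined for anyone with at least one scheduled call. With S = 14 the pattern is the same: 7 completed calls give 14/7 = 2.0 as written, against 50%.

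**The arm of 15, assumed pattern.** Suppose that 12 patients take all 10 calls, 2 take 5 and 1 takes none. This pattern is only an illustration. Scheduled calls are 15 × 10 = 150. Completed calls are 12 × 10 + 2 × 5 + 0 = 130.

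- Pooled, as written: 150/130 = 1.15. Pooled, C / S: 130/150 = 86.7%.
- Mean per patient, as written: (12 × 1 + 2 × 2)/14 = 1.14, over 14 patients because one has no value. Mean per patient, C / S: (12 × 1 + 2 × 0.5 + 0)/15 = 86.7%, over all 15.

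The direction is therefore wrong in both forms. Only the per-patient form also loses a patient. The pooled figure can be inverted back exactly (130/150). The reciprocal of the per-patient mean, 14/16 = 87.5%, recovers neither the mean over all 15 (86.7%) nor the mean over the 14 with a value (13/14 = 92.9%).

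**The case against.** The strongest reply is that this is a slip which no competent analyst would follow. The outcome is called adherence, the telemonitoring definition shows the intended direction, and either ratio needs the same two counts, so the intended figure can be computed whenever both are kept. That stands as a comment on practical risk. It does not make the sentence right: it is the only definition of this outcome in the article, and followed literally it gives the wrong direction.

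Three stronger readings are tempting, and the article does not support them.

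- A reader might infer that the least adherent patients necessarily drop out of the summary. That needs a per-patient ratio. The text does not say whether the ratio is per patient or pooled, and a pooled ratio stays defined unless no call at all is completed.
- A reader might infer that one or two patients could reverse the conclusion on whether the coaching can be delivered. The article states no adherence threshold that could be crossed, and Statistical methods plans a descriptive analysis.
- A reader might infer that the number of scheduled calls is itself contradictory, because the specifications table says "once a week for the initial month, followed by sessions every two weeks" whereas the Intervention group section says twice a month. At month 4, the time point in Table 2, the two agree. Four months are about 17.3 weeks, which leaves about 13.3 weeks after the first 4. That holds 6 full two-week intervals, so 4 + 6 = 10 calls under either phrase. At month 6 the answer depends on rounding: 26 weeks give 4 + 22/2 = 15, but the 180-day horizon gives (180 − 28)/14 = 10.9, or 10 full intervals, and so 14 calls under both phrases.

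Whether a call reached at the second attempt counts as completed, and how time after death or withdrawal is treated, are details that a condensed article may leave to the full protocol or analysis plan. They are not part of this point.

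**Conclusion.** The definition is wrong as written. Set against its neighbours, it is scheduled over completed calls: 1 at perfect adherence, 2.0 when half the calls are completed, and larger as adherence worsens. This holds for a pooled and for a per-patient ratio. The undefined value for a patient with no completed call arises only if the ratio is per patient.

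The consequence is limited to the reporting and interpretation of one feasibility outcome. No sample size, power or stated decision threshold depends on it. The count of 10 calls by month 4 rests on a 4-week first month, and the 15-patient pattern is an assumption. The direction of the error depends on neither.

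**What to change.** Replace the definition with: the number of coaching calls completed relative to the number scheduled, up to T2 (4 months) as marked in Table 2. It then lies between 0 and 100% and can be read beside telemonitoring adherence in the same direction. If the ratio is meant per patient, a patient with no completed call then scores 0% and stays in the summary.

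The cost is one sentence. Both counts are already needed for the written definition, so no additional data have to be collected, and nothing else in the design has to change.
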